# Study protocol for a cluster-randomized trial to compare human papillomavirus based cervical cancer screening in community-health campaigns versus health facilities in western Kenya

**DOI:** 10.1186/s12885-017-3818-z

**Published:** 2017-12-06

**Keywords:** Cervical cancer screening, Community health campaigns, Kenya, HPV self-collection, Implementation science

## Abstract

**Background:**

Despite guidelines for cervical cancer prevention in low-resource countries, a very small proportion of women in these settings undergo screening, and even fewer women are successfully treated. Using pilot data from western Kenya and World Health Organization recommendations, we developed a protocol to implement evidence-based cervical cancer screening and linkage to treatment strategies to the rural communities. We describe the protocol for a cluster-randomized trial to compare two implementation strategies for human-papillomavirus (HPV)-based cervical cancer screening program using metrics described in the RE-AIM (reach, efficacy, adaption, implementation and maintenance) framework.

**Methods:**

The study is a three-year, two-phase cluster-randomized trial in 18 communities in western Kenya. During Phase 1, six control communities were offered screening in health facilities; and six intervention communities were offered screening in community health campaigns. Screening was done with human-papillomavirus testing through self-collected specimens. Phase 1 ended and we are working in partnership with communities to further contextualize the implementation strategy for screening, and develop an enhanced linkage to treatment plan. This plan will be tested in an additional six communities in Phase 2 (enhanced intervention). We will compare the reach, efficacy, cost-effectiveness and adaptability of the implementation strategies.

**Discussion:**

Effective low-cost cervical cancer prevention technologies are becoming more widely available in low- and middle-income countries. Despite increasing government support for cervical cancer prevention, there remains a sizeable gap in service availability. We will use implementation science to identify the most effective strategies to fill this gap through development of context-specific evidence-based solutions. This protocol design and results can help guide implementation of cervical cancer screening in similar settings, where women are most underserved and at highest risk for disease.

**Trial registration:**

This trial is registered at ClinicalTrials.gov, NCT02124252.

**Electronic supplementary material:**

The online version of this article (10.1186/s12885-017-3818-z) contains supplementary material, which is available to authorized users.

## Background

Despite the fact that cervical cancer is highly preventable through vaccination and organized screening programs, over 500,000 women worldwide are diagnosed with the disease every year [1]. About 9 out of 10 cervical cancer deaths occur in low-resource countries, with a particularly high burden in sub-Saharan Africa, where the mortality rate is 85% [2, 3]. The inequality between high and low-resource countries is mainly due to lack of screening in low-resource countries, which lack the health care infrastructure required for the cytology-based screening programs that have dramatically reduced the disease burden in wealthier countries. The World Health Organization (WHO) recommends alternative cervical cancer prevention techniques and protocols for low-resource countries that employ low-cost or simple-to-use screening technologies [4]. One such strategy – high-risk human papillomavirus (HPV) testing– has been shown to reduce the incidence and mortality from cervical cancer when coupled with outpatient treatment for women with HPV-positive results [5].

In addition to effective screening tools, the impact of cervical cancer prevention programs depends on two main context-specific factors: (1) women’s access to screening and (2) successful acquisition of treatment for women who screen positive. Access to both screening and treatment is most challenging in poor rural areas, due to geographic and infrastructure constraints [6, 7]. Most health care in rural areas takes place in small health facilities with limited space, staffing, and equipment, making it challenging to implement same-day “screen & treat” strategies that have been proposed to overcome barriers to treatment access [8]. So, despite the development of guidelines for cervical cancer screening that employed evidence-based technologies and lower resource protocols, the lack of rigorously tested, context-specific implementation strategies has left a gap between policy and practice.

In order to develop a context-specific, sustainable implementation strategy, we undertook formative work to identify local barriers and facilitators for cervical cancer screening in government-supported health facilities in rural western Kenya, an area of East Africa with a high cervical cancer burden and screening rates as low as 3% [9, 10]. We found that access to screening was limited by lapses in service availability and lack of clinic attendance for preventive care [11]. When services were available, both providers and patients found the need for a pelvic exam limited the acceptability of cervical cancer screening. Based on the facility-based barriers, we developed and piloted a highly successful community health campaign model for screening, consisting of outreach followed by a brief campaign held in a central site in the community, offering on-site screening and referrals for treatment [12]. An advantage of community-based screening is that only screen-positive women need to visit health facilities for follow-up care, reducing the visit burden for both woman and facilities, and allowing resources to be directed toward strategies to increase treatment uptake, such as intensified follow-up, transportation assistance or mobile units that bring treatment to remote villages. Thus, as has been seen in other health services [13–15], by combining community-screening with enhanced linkage strategies, our approach could maximize the health impact by increasing the number of women screening *and* the proportion successfully accessing treatment.

To address the reluctance around pelvic exams, we chose to offer screening with self-collected specimens for HPV testing, an evidence-based strategy that would eliminate pelvic exams for initial screening, further increasing screening acceptance and efficiency. We developed a study protocol that will allow us to compare two context-specific implementation strategies for an HPV-based cervical cancer prevention program through a cluster-randomized trial of HPV-based cervical cancer screening in community-health campaigns versus health facilities using the RE-AIM framework [16, 17]. This paper describes the study protocol (V 3.0, 20 July 2017) and the plan to evaluate the adaptability, comparative effectiveness and cost-effectiveness of these two strategies.

## Methods

### Study design and setting

The study is a two-phase cluster randomized trial in western Kenya to evaluate reach, effectiveness, cost-effectiveness and maintenance of two implementation strategies for a cervical cancer prevention protocol that consists of four critical, evidence-based components:
**HPV and cervical cancer outreach and education**
*.* In western Kenya, we found that women’s baseline knowledge and perception of cervical cancer risk is low; a brief educational intervention provided by community health workers in primary care clinics improved these baseline factors and increased women’s intention to screen [18].
**HPV-testing using self-collected specimens with referral for treatment based on a single positive result.** An HPV-based screening strategy is effective at reducing incidence of cervical pre-cancer and invasive cancer when women with screen-positive results undergo cryotherapy [5, 19, 20]. Self-collected specimens are highly accurate, with comparable results to provider-collection for the detection of high-grade cervical precancer [21–23] Women have consistently found self-sampling acceptable and preferable to provider-testing [24–26]; this finding has been supported in studies from sub-Saharan Africa [27, 28]. Studies in various countries have shown that a self-collection strategy increases screening uptake by women not attending clinics [29–34].
**Notification of screening results using text messaging.** Based on our prior experience with mobile health interventions [35, 36] and the high rates of cell phone use in western Kenya [37], HPV test results were sent to all women via text message with instructions about appropriate follow-up as recommended by the Kenya Ministry of Health guidelines.
**Treatment with cryotherapy unless contraindicated by cervical exam.** Cryotherapy is a low-cost, effective treatment method that can be safely carried out by mid-level providers in low-resource settings [38, 39]. Women who are not candidates for cryotherapy (i.e. lesions too large or abnormal cervical anatomy) were offered Loop Electrosurgical Excision Procedure carried out in the County Hospital. Together, HPV testing followed by cryotherapy for women who test positive reflect the current WHO recommendations [40].

In Phase 1 of this study, we compared two implementation strategies that incorporated these four evidence-based elements of screening. Based on our preliminary data, we found that reaching and attending a health facility for preventive care was a significant barrier to screening for many women. Therefore, the main objective was to compare a model offering screening in brief, high throughput community health campaigns to that of a standard of care in which screening was offered in local health facilities using the metrics defined in the modified RE-AIM framework.

In Fig. 1, we present an overall schema of the cluster-randomized trial. In Phase 1, six communities were randomized to the intervention: HPV screening carried out in **community health campaigns**. The remaining six were comparison communities: HPV testing offered in **government health facilities**. HPV-test positive women in all communities were referred to the County hospital for immediate treatment, which is considered standard linkage to treatment.

**Fig. 1 Fig1:**
[figure not shown]
Two-phase cluster-randomized trial design

Development of an enhanced strategy for linkage to treatment: After Phase 1, we have an “inter-phase intervention development” period in which we are evaluating the results from the trial. The outcomes from the qualitative and quantitative measures will be used to refine the screening intervention using context-specific details and develop an enhanced strategy for linkage to treatment. Although we have identified factors that enable and inhibit women’s access to treatment, we chose to wait until after Phase 1 for the development of the enhanced strategy for linkage to treatment in order to truly work in partnership with the community. The delayed development of the linkage to treatment strategy has allowed us obtain a baseline measure of the efficacy of standard referrals and identify factors that would influence women’s access to care in this setting.

After developing the strategy for enhanced linkage, we will pilot and then test the linkage to treatment strategy as part of an “enhanced intervention” in the six communities that served as controls in Phase 1. Using these communities for the enhanced intervention increases the efficiency of the study in two ways: i. we will have done community enumeration and engagement, and ii. we will compare linkage to treatment outcomes from these “enhanced intervention” communities to the intervention communities from Phase 1.

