**Fig. 2 Fig2:**
[figure not shown]
Map of communities randomized to control and intervention activities in Migori, County Kenya. This map was developed by [name], who has provided written permission for use in this publication

#### Intervention development and cluster randomized trial: Phase 2

**Enhanced linkage to treatment:** We will work with health care providers, community members and other stakeholders to review outcomes from the quantitative, qualitative and process measures in Phase 1, critically examine and modify the cervical cancer *screening* strategy to develop and pilot the enhanced linkage to *treatment* intervention over a 6–9 month period between Phase 1 and 2. We will do this through a series of key stakeholder meetings, followed by the establishment of smaller working groups for the creation of the specific intervention components. In the first set of meetings, we will present the findings from Phase 1 and seek feedback on representativeness and discuss implications for culturally relevant intervention strategies. Options for the most feasible and acceptable strategies to increase the number of women linking to treatment will be explored in the light of that data.

Criteria for potential strategies include: community-developed, low-cost, feasible in all study communities, and able to ensure treatment for HPV-positive women in a timely manner in accordance with Ministry of Health guidelines. In a second, small stakeholder meeting, we will review potential strategies discussed and developed in the first meeting, and discuss solutions proposed in other settings, including the use of mobile treatment units, transportation vouchers, and treatment “navigators” to help women understand and travel to treatment sites. Once the linkage intervention has been defined, we will hold another working group with stakeholders to create a standardized protocol, training manual, standard operating procedures and data collection instruments. After equipment procurement, provider training and further outreach messaging, the enhanced linkage strategy will be piloted in two to three Phase 1 intervention communities prior to launch of Phase 2.

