#### Primary and secondary endpoints

To determine the **reach** of cervical cancer screening using HPV-testing in community health campaigns compared to clinics, we are using the following metrics: i) the absolute number of women who completed screening in each arm and ii) the proportion of women in each arm who completed screening. The total number of women in each arm is the number of women 25–65 in each community as determined by census data. Secondary outcomes will include iii) the proportion of women who accept screening among women offered at each site and iv) the proportion of women in the clinic-based arm who request clinician-collected specimens.

To determine the **efficacy** of a community-developed strategy to increase treatment access, we will compare the efficacy of the community-based HPV testing with standard versus enhanced linkage to treatment using the following metrics: i) the number of women who receive treatment after screening HPV + in the intervention (Phase 1) compared to the enhanced intervention (Phase 2) and ii) the proportion of HPV-positive women in each arm who complete treatment. Secondary outcomes that address quality of care concerns for the models will include iii) the proportion of women who receive the correct treatment (per Ministry of Health protocol) during a single treatment visit and iv) the average time between HPV testing and access of treatment by arm.

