#### Cost-effectiveness analysis (maintenance)

We assessed the costs, population health impact, and incremental cost effectiveness of three intervention strategies (clinic-based screening with standard linkage to treatment; community screening with standard linkage; and will assess community screening with enhanced linkage). To do this, we undertook a micro-costing of the resources needed to carry out the activities in both arms in Phase 1 and 2. Costing included 1) personnel (including fringe benefits); 2) recurring supplies and services; 3) capital and equipment; and 4) facility space. Intervention costs were assessed using a uniform cost data collection protocol to quantify resources used and associated costs in each of the study sites (community-health campaigns, clinics, laboratories and district hospitals). Data was obtained through administrative record review and interviews with administrative, finance and human resources staff, supplemented by direct observation in a limited number of staff “time and motion” studies in order to distinguish cervical cancer-related activities from other health services delivered by the same personnel. Costs were summarized as total program costs as well as costs per woman screened and per HPV positive women treated.

We observed study outcomes to estimate the health outcomes associated with each screening and linkage strategy. Observed data include will include the number of women screened and treated for high-risk HPV, the proportion of women undergoing cryotherapy vs. LEEP, and the side effects associated with each treatment. We will find the best possible available data to estimate the prevalence of various HPV-subtypes in the region, and the associated risks of cervical intraepithelial neoplasia (CIN), recurrence rates of CIN after treatment, and invasive cancer in women with and without treatment. We will translate each health event into a standard metric of burden of disease, Disability-Adjusted Life Years (DALYs), which combines morbidity (and associated disability) with premature mortality (lost “life years”).

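### Screening is to be refined along with linkage before Phase 2, so the Phase 2 versus Phase 1 contrast estimates a package and cannot isolate the linkage effect

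*Protocol article*

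**What the plan says.** Three places in the protocol article announce that screening itself will change between phases.

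- Abstract, Methods: the team is working with communities to "further contextualize the implementation strategy for screening, and develop an enhanced linkage to treatment plan".
- Study design and setting (text after Fig. 1): Phase 1 outcomes "will be used to refine the screening intervention using context-specific details and develop an enhanced strategy for linkage to treatment".
- Intervention development and cluster randomized trial, Phase 2: stakeholders will "critically examine and modify the cervical cancer" screening strategy in the course of developing the linkage intervention.

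Study design and setting then says the team will "test the linkage to treatment strategy as part of an “enhanced intervention” in the six communities that served as controls in Phase 1", and gives the comparator: "we will compare linkage to treatment outcomes from these “enhanced intervention” communities to the intervention communities from Phase 1".

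Three other places name only linkage as the difference.

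- Implementation framework, second hypothesis (efficacy): a community-driven intervention improves linkage among HPV-positive women relative to standard referral.
- Primary and secondary endpoints: "we will compare the efficacy of the community-based HPV testing with standard versus enhanced linkage to treatment". Metric i is the number of women treated after a positive test. Metric ii is the proportion of HPV-positive women who complete treatment.
- Cost-effectiveness analysis: the strategies include "community screening with standard linkage; and will assess community screening with enhanced linkage", with community screening named identically in both.

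The Statistical analysis section gives the efficacy model as Poisson with a log link and an offset for community size.

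**The concern.** A comparison named for linkage should differ in linkage. Here the campaign may differ too, and nothing in the article holds it at its Phase 1 form or runs the refined campaign with standard referral. In every Phase 2 community the two changes arrive together, so no later analysis can separate them. This is distinct from the phases being non-concurrent and from earlier exposure of the Phase 2 communities. It would remain with concurrent phases in fresh communities.

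At stake is attribution. A gain in women treated, and the incremental cost-effectiveness ratio (ICER) between the two community strategies, would naturally be reported as the effect and value of enhanced linkage when part could come from a better campaign. A programme deciding whether to pay for linkage support would be using the wrong estimate.

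**Working it through.** **1. The plan's own figures.** Sample size gives about 1000 eligible women per community, 600 attending a campaign (60%) and 510 screened.

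- Uptake among attenders: 510/600 = 85%.
- Six campaign communities: 6 × 510 = 3060, which agrees with the stated total.

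The section gives no HPV prevalence and no expected treatment proportion.

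**2. Metric i and the offset model.** Women treated = eligible women × reach × HPV prevalence × proportion of HPV-positive women treated. An offset for community size divides out the number of eligible women and leaves

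rate ratio = (reach ratio) × (prevalence ratio) × (treated-proportion ratio).

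Only the last factor is linkage. Set it and the prevalence ratio to 1, meaning no linkage effect. The rate ratio then equals the reach ratio:

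| Screened in Phase 2 (assumed) | Ratio to plan | Apparent gain in women treated |
|---|---|---|
| 540 per community (90% of 600 attenders) | 540/510 = 1.059 | +5.9% |
| 600 per community | 600/510 = 1.176 | +17.6% |
| 4500 in total (Phase 1 resource ceiling for the campaign arm) | 4500/3060 = 1.471 | +47.1% |

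These percentages do not depend on prevalence or on the treated proportion. For scale, at an assumed 30% prevalence and 50% treated, 3060 × 0.30 × 0.50 = 459 women treated becomes 486, 540 or 675.

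Reaching 600 needs either every one of the 600 attenders to accept, or attendance of 600/0.85 = 706 of 1000 at unchanged uptake. The middle row is therefore a sizeable improvement, and the last row is an upper bound set by resources, not a forecast.

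**3. Metric ii.** The denominator is HPV-positive women, so reach does not move it mechanically. Two indirect routes remain: a different mix of women attending, and changed education, since the module described under Phase 1 covers available treatment. For case mix, suppose 50% of the original group are treated and the refined campaign adds a fraction f of extra HPV-positive women, of whom a proportion p are treated. With linkage unchanged the overall proportion is (0.50 + f × p)/(1 + f):

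| f | p = 0.70 | p = 0.30 |
|---|---|---|
| 0.10 | 51.8% | 48.2% |
| 0.20 | 53.3% | 46.7% |
| 0.47 | 56.4% | 43.6% |

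All these inputs are assumptions. The table shows that the shift can go either way. It does not estimate its size.

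**The case against.** The strongest reply is that implementation trials legitimately test packages, and that this article half says so. Linkage is tested as part of an enhanced intervention, metric i is worded as intervention against enhanced intervention, and the fourth hypothesis concerns community screening with enhanced linkage as a whole. The ICER is defined between strategies and is nowhere assigned to linkage alone. Refining the campaign with the community is a stated purpose of the inter-phase period. The refinement may also be small: the linkage options listed are mobile treatment units, transport vouchers and navigators, and the sentence on modifying screening can be read as change made to serve linkage. The proportion of women who receive their results is already a process measure.

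Much of this stands. It is why the remedy is to say package consistently, and why freezing the campaign is not required. It does not remove the conflict: the second hypothesis, the lead sentence of the efficacy endpoints and the strategy names still credit linkage, and metric i and the offset model still absorb reach.

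A reader might go further and infer that the trial can say nothing about linkage, that both efficacy metrics are inflated, or that better result notification or specimen handling will pass as linkage efficacy. The document does not support this. Metric ii conditions on HPV-positive women, and its bias has no known sign. No section announces a change to notification or specimen handling. Implementation consistency lists notification as a component separate from linkage, but the result message carries follow-up instructions, so where linkage begins is open to argument. A shift in receipt of results would be visible in the planned process data.

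**Conclusion.** The concern holds in a limited form. The screening changes are announced three times, the contrast is labelled as linkage three times, and no arm separates them, so the linkage effect cannot be isolated.

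For the number treated and the community-size model the consequence is direct: with no linkage effect, a rise from 510 to 600 screened per community gives +17.6%, and the assumptions tried run from +5.9% to +47.1%. For the proportion of HPV-positive women treated it is indirect and cannot be sized or signed from the document.

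This rests on two readings: that the screening refinement is more than nominal, since its extent is not stated, and that the efficacy model applies to the Phase 2 contrast. The Statistical analysis section names community versus clinic testing and labels the Poisson model only as efficacy.

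The Phase 1 comparison of campaigns with facilities is untouched. The correction is worth making because it changes what the trial may conclude, but the flaw does not invalidate the trial.

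**What to change.** 1. In the second hypothesis (Implementation framework), the efficacy paragraph of Primary and secondary endpoints, and the Cost-effectiveness analysis, state that the Phase 2 versus Phase 1 contrast and its ICER estimate a combined package: refined campaign plus enhanced linkage against original campaign plus standard referral.
2. Rest any inference about linkage on treatment completion with HPV-positive women as the denominator, and use that denominator, not community size, in the corresponding model. Keep the number treated as a measure of the whole package.
3. Report completion also among HPV-positive women who received their result, using the receipt data already planned under Process measures. This should accompany the main proportion, not replace it: if the linkage strategy itself improves delivery of results, the restricted figure omits part of its effect.
4. Record each change made to screening between phases, so that readers can judge how far the package differs from the Phase 1 campaign.

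If the sponsor wants a linkage-only claim, holding the screening components at their Phase 1 form during Phase 2 would support it as far as this problem goes. That would leave screening refinements untested in this trial, so it is a trade-off for the sponsor to weigh.

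The cost is protocol wording, a change of model denominator and a short log, with no extra participants. Trial status shows the linkage strategy still being designed, so the changes can precede Phase 2. The downside is that the efficacy claim is narrowed to the package.
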